### Primary outcome

The primary outcome is the average daily UVR D-to-F (standard erythemal dose (SED)), across 21 consecutive days between June and July 2018 (t1), following completion of six out of seven intervention sessions by the intervention group. UVR D-to-F is estimated by combining data from a UVR dosimeter worn on the wrist (SunSaver 3, Bispebjerg Hospital, Copenhagen, Denmark)^19^ and the patient’s photoprotective activities, self-reported using the daily UVR protection diary. The dosimeter was set to measure UVR levels every 5 s and record the average every 5 min, which has been validated as providing reliable measurements of total UVR exposure over the course of a day.^20^ The combination of the daily UVR protection diary and dosimeter to estimate UVR D-to-F has been used in our earlier research with this population (Phase One) and demonstrated to function sufficiently well to be the primary outcome in this trial. The paper-based daily UVR protection diary allows participants to record periods of time spent outside (in 15 min intervals) and the timing of any specific photoprotection activities while outside (ie, wearing a face visor, hat, hoodie worn-up, glasses, scarf or face buff or applying sunscreen and lip block) by drawing a line on a grid (see online supplementary file 1). To avoid errors in recording, each participant will receive training on how to complete the diary. UVR D-to-F will be calculated using the dose recorded at the wrist weighted by the level of protection provided by the combination facial photoprotection behaviours used.^5^

10.1136/bmjopen-2018-028577.supp1Supplementary data

### Secondary outcomes

The following outcomes relate to between-group comparisons in 2018 and are recorded on the daily UVR protection diary. UVR-related outcomes also use data from the dosimeter.Average daily UVR D-to-F across 21 consecutive days in August 2018 (t2). This is to investigate the stability of any improvement identified in the primary outcome period (June to July 2018), as it will be 4–6 weeks after the main intervention and follows session 7 (the booster session).Average daily total UVR exposure during each of the 21 day periods (t1, t2) and the average daily time outside across all daylight hours and restricted to 11:00–15:00, when UVR levels are at their highest. These data will be gathered from the dosimeter and the UVR protection diary.Average daily proportion of time outside across daylight hours and between 11:00 and 15:00 with ‘very good’ or ‘excellent’ face photoprotection during each of the 21 day periods (t1, t2). The categorisations relate to the Daily Photoprotection Scale (DPS)^3^ developed for the Phase One n-of-1 study in consultation with the UK XP clinical team. Facial photoprotection activities (excluding sunscreen) are ranked according to their relative level of photoprotection. The following combinations are classed as ‘very good photoprotection’: hat, glasses and scarf/buff; hat, glasses, scarf/buff and hoodie. ‘Excellent photoprotection’ is wearing a face visor, which completely covers the face.Average daily proportion of time outside across daylight hours with sunscreen protection, defined as when sunscreen was applied within the previous 3 hours, during each of the 21 day periods (t1, t2).Average daily number of times sunscreen is applied irrespective of time outside during each of the 21 day periods (t1, t2).Average daily measures of mood, automaticity of photoprotection activities, prioritisation of photoprotection compared with other priorities and level of self-efficacy to manage barriers during the two follow-up periods (t1, t2) will be assessed. The single items have been adapted from ecological momentary assessment questions used in our n-of-1 study^3^ (eg, How much do you agree that UVR protection of your face today was something you did automatically without thinking (0=strongly disagree to 10=strongly agree)) and are included on the UVR protection diary (see online supplementary file 1).

### Tertiary outcomes

The following outcomes are assessed once, at the start of each 21 day period (t0, t1, t2, t3). Health-related quality of life (HRQoL), psychological well-being, automaticity of photoprotection activities, self-efficacy in the context of barriers and self-rated photoprotection adherence will be measured using self-report questionnaires. Data will be combined across t1 and t2 to assess proximal impact of the intervention and t3 will be used to assess stability of impact.

See table 1 for the schedule of self-reported measures.HRQoL will be assessed using the EQ-5D-5L^21^Emotional well-being will be measured by the Short-form Warwick Edinburgh Mental Well-Being Scale (SWEMWBS)^22^Automaticity of photoprotection activities will be assessed using the 4-item Self-Report Behavioural Automaticity Index (SRBAI),^23^ adapted to photoprotection. It is a validated subscale of the Self-Report Habit Index^24^ which focuses on the automaticity of behaviour. It asks respondents to rate the extent to which they agree with each statement on a seven-point Likert-type scale (eg, UVR photoprotection is something I do without thinking (1=strongly disagree to 7=strongly agree)). The average of responses gives a score between 1 and 7, with higher scores indicating greater automaticity.Self-efficacy to photoprotect will be measured using a 21-item scale (Photoprotection Self-Efficacy Questionnaire (PhotoSEQ)) developed for this study, as no validated questionnaire specific to photoprotection activities in the presence of barriers, as recommended by Bandura,^25^ was identified (see online supplementary file 2). Three items ask the respondent to rate their level of confidence that they can carry out a type of photoprotection activity (eg, shifting timing and/or duration of outdoor activity, photoprotection using clothing, correctly apply sunscreen) on a 10-point scale (0=Not at all – 10=very confident); two items ask separately about confidence to wear photoprotective clothing and apply sunscreen in the presence of nine different barriers in the following 4 weeks (eg, How confident are you that you can photoprotect even if/when: unexpected things get in the way). Two subscales are calculated, an average self-efficacy score for sunscreen and similarly for photoprotective clothing and shifting time/duration of activity. Higher scores indicate greater self-efficacy.A secondary brief measure of photoprotection activities was developed to assess photoprotection to indicate whether improvements in photoprotection are maintained, when participants will not be completing the daily UVR protection diary at t3 (see online supplementary file 3.). To allow comparison with the diary, it will be completed at all follow-up points. The Brief Photoprotection Adherence Questionnaire (BPAQ) has five items and assesses duration of time outdoors, and photoprotection used when outdoors during the previous 7 days. Three items assess different ways of protecting outdoors: how often respondents wore protective clothing (eg, When you went outside, how often did you protect your face against UVR using protective clothing? (0=never to 10=all the time)); the number of days sunscreen was applied in the morning (0–7 days); and how often sunscreen was reapplied when outdoors for longer periods (0=not at all to 10=always). Two items ask respondents to estimate average duration of time outdoors each day (Never, <30 min, 31 min–1 hour, 2 hours, upwards in hourly intervals to >8 hours) and average duration of time outdoors each day between 11:00 and 15:00 when environmental UVR levels are highest. Each item will be analysed separately.
10.1136/bmjopen-2018-028577.supp2Supplementary data
10.1136/bmjopen-2018-028577.supp3Supplementary data

**Table 1 T1:** Summary of self-reported measures schedule

	Intervention and control groups 2018				Delayed intervention group only 2019		
	Baseline (t0) (April)	Follow-up (t1) (June–July)	Follow-up(t2) (August)	Follow-up (t3) (December)	Follow-up (t4) (April)	Follow-up (t5) (June– July)	Follow-up (t6) (December)
UVR Protection Diary	✓	✓	✓		✓	✓	
EuroQol five dimensions questionnaire (EQ-5D)	✓	✓	✓	✓	✓	✓	✓
Short-form Warwick-Edinburgh Mental Well-Being Scale (SWEMWBS)	✓	✓	✓	✓	✓	✓	✓
Self-Report Behavioural Automaticity Index’ (SRBAI)	✓	✓	✓	✓	✓	✓	✓
Photoprotection Self-efficacy Questionnaire (PhotoSEQ)	✓	✓	✓	✓	✓	✓	✓
Brief Photoprotection Adherence Questionnaire (BPAQ)	✓	✓	✓	✓	✓	✓	✓
Service Use Questionnaire (SUQ)	✓			✓	✓		✓
Feedback questionnaire (intervention group only)		✓				✓	

Further exploratory analyses will examine change from baseline incorporating the delayed intervention group allowing for higher power to assess intervention-related changes. These will be undertaken unblinded to group allocation after main efficacy analyses are complete.

### The XPAND intervention

XPAND is composed of a combination of one-to-one sessions and materials purposely designed to target barriers to photoprotection. It was designed to be delivered by a healthcare professional (HCP) without specialist psychological training (eg, clinical nurse specialist). In the trial context, facilitators will be two psychologists and a research nurse.

#### One-to-one sessions

Facilitators will deliver 7x one-to-one sessions to each participant. Further information on the structure of the intervention is available in figure 2. Each session will include a combination of personalised and generic content. The intervention content and techniques were systematically developed and selected using intervention mapping.^12^ Core strategies delivered to all participants will include those to increase self-efficacy, self-regulatory skills and the automaticity of photoprotection. In addition, personalised modules will be delivered, as needed, selected initially based on data collected in Phase One studies and a profiling questionnaire, and iteratively as additional barriers emerge during the sessions. The facilitators will use a communication style consistent with motivational interviewing.^26^ They will be guided by a manual, including theory-based behaviour change methods mapped to recognised taxonomies,^12 27^ and specific techniques from other therapeutic approaches (eg, Acceptance and Commitment Therapy).^28^

**Figure 2 F2:**
[figure not shown]
Structure of the XPAND intervention.

#### Intervention materials

Patient-facing materials have been developed and will be provided to participants in session one and used throughout the intervention to facilitate discussion, provide real-life examples and reinforce the concepts and skills discussed during the sessions. These are summarised in figure 2.

### Sample size calculations

The target sample size for the study is a total of 24 patients (ie, 12 per group), which was based on the ability to detect an average daily UVR D-to-F difference of 0.10 SED between the groups during the June to July 2018 assessment period. This difference was considered clinically meaningful and potentially achievable due to the personalised nature of the intervention. From our Phase One study of UVR exposure, the average daily UVR D-to-F for people diagnosed with XP was 0.27 SED (SD=0.14), with a within-person correlation of *r*
_ICC_=0.31. Thus, the anticipated difference relates to an effect size of d=0.73, or just over a one-third reduction in average daily UVR D-to-F. Adjusting for the design effect due to the dependence of assessments within individuals, a sample size of 20 patients with 21 daily observations has 80% power to detect a reduction of 0.10 SED in average daily UVR D-to-F at the 5% significance level. Accounting for attrition of 20%, based on our previous research, the target sample size was set at 24.

### Statistical analyses

The main efficacy analyses will be conducted by the trial statistician (SN) following a prespecified analysis plan and blind to group allocation. The analysis will follow the intention to treat principle with individuals analysed within the groups to which they were randomised irrespective of whether they received or persisted with the intervention.

The treatment effect on the primary outcome of daily UVR D-to-F over 21 days between June and July 2018 and secondary outcome of daily UVR D-to-F over 21 days in August will be estimated simultaneously using a linear mixed model. Given the skewed distribution of UVR D-to-F, a logarithmic transformation will be applied and robust SE will be estimated. A random intercept will account for the repeated assessments of UVR D-to-F within individuals across all 42 days, with an autoregressive error structure to account for correlation between assessments across successive days. In addition to the dummy-coded group variable, other covariates in the model include a dummy-coded variable for the assessment period (June–July vs August), an assessment period by group interaction, the patients baseline average daily UVR, an indictor variable for the patients propensity to burn and the background level of UVR recorded by the observatory closest to the patients’ house on the day. Data will be summarised as the empirical Bayes estimate of the average daily UVR D-to-F in SEDs for each assessment period for each group.

This approach allows for missing daily data within each individual under the assumption that data are missing at random. We will run sensitivity analyses to explore the influence of missing data on the effect estimates, so as to allow for a consideration of the likely plausible range for the treatment effect under a number of missing not at random assumptions. For average daily assessments, where these are not available for the full 21 days, this will involve imputing missing values under a range of conservative assumptions using the average daily values of the group to which the individual is assigned using a pattern mixture model approach (eg, average daily level +0.0 SED to 0.5 SED).

Treatment effects for average daily levels of mood, self-efficacy, goal priority, automaticity and time outside will be analysed for both assessment periods simultaneously using mixed-effects as described above. Treatment effects for adherence, self-efficacy, automaticity, HRQoL and psychological well-being taken at the start of the June and August assessment periods will also be estimated using linear mixed models but will specify an unconstrained error structure. It is not anticipated that transformation will be required to account for skew in any of these outcomes; however, robust SE will be estimated. Covariates included in the analysis will be the same as above except that baseline levels of the outcomes will be included in place of baseline average daily UVR D-to-F. Scale scores will be calculated using proration to account for missing items within the scale where there is at most one-third of items missing. For example, where scale includes six items, at least four items must have been completed. Otherwise, the scale score will be set to missing for that individual.

Further exploratory analysis using dynamic regression models will evaluate changes in both level and variability in daily UVR exposure over time between March and September, accounting for treatment using a regression discontinuity approach. This is possible as the dosimeter will be worn for the entire period. However, due to patient burden and since the UVR protection diary is only completed for 3-week intervals, it will also be necessary to calculate UVR D-to-F using average daily photoprotection during the pre and post diary intervals. This differs from the main analysis where UVR D-to-F is calculated directly based on photoprotection activities recorded on the diary.

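### Robust standard errors with only 19 to 24 patients: unless a small-sample correction with t-type degrees of freedom is applied, the nominal 5% primary test runs at about 8–10%

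*Protocol article*

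**What the plan says.** The Statistical analyses section of the protocol article fits one linear mixed model to daily UVR dose to the face in the June–July and August periods. Because the outcome is skewed, "a logarithmic transformation will be applied and robust SE will be estimated". The covariance model is also given: "A random intercept will account for the repeated assessments of UVR D-to-F within individuals across all 42 days, with an autoregressive error structure". Besides group and period, the covariates include "an assessment period by group interaction, the patients baseline average daily UVR, an indictor variable for the patients propensity to burn", plus the background UVR on the day.

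For the remaining diary and questionnaire outcomes the same section expects no need for a transformation, "however, robust SE will be estimated".

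The Sample size calculations section states that "a sample size of 20 patients with 21 daily observations has 80% power to detect a reduction of 0.10 SED", with testing at the 5% level. On the planned number it adds: "Accounting for attrition of 20%, based on our previous research, the target sample size was set at 24". The Randomisation section allocates members of one family together, without saying how many families there are.

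The article names no variant of the robust estimator, no finite-sample correction, no degrees of freedom, no reference distribution and no choice between ML and REML. It refers to a prespecified analysis plan, which is not shown.

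**The concern.** The sandwich variance is justified as the number of independent units grows large. Here the independent units are patients, or families where relatives are randomised together. There are at most 24 of them. Three patient-level terms (group, baseline UVR, propensity to burn) and an intercept are estimated from those units, which leaves about 15 to 20 between-patient degrees of freedom.

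In this setting the plain sandwich is too small on average, because fitted residuals are smaller than true errors. It is also variable, so a normal cut-off of 1.96 is too low. Both faults push the same way: too many false positives, and 95% intervals that cover less than 95%. One test carries the primary efficacy claim, and the abstract links success to adoption into routine care.

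**Working it through.** **1. The plan's own figure.** Inputs from Sample size calculations: d = 0.73, within-person correlation 0.31, 21 days, 5% level (two-sided assumed).

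- Variance factor for a 21-day mean: (1 + 20 × 0.31)/21 = 7.2/21 = 0.343.
- Patients per arm, normal approximation: 2 × (1.960 + 0.842)² × 0.343/0.73² = 10.1, so about 20 in total.
- Power at 10 per arm, normal reference: 79.6%, which matches the stated 80%.
- Power at 10 per arm, t reference on 18 degrees of freedom: 75.1%.

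The stated figure therefore matches a large-sample calculation. This does not show which reference the analysis will use.

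**2. Number of units.** 24 × 0.8 = 19.2, so about 19 patients after 20% attrition; the article's own calculation uses 20. With four patient-level parameters, G − 4 = 15, 16 and 20 for G = 19, 20 and 24.

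**3. Simulation of the stated model with no treatment effect.** Seven fixed effects, a random intercept, first-order autoregressive errors, 42 days per patient and correlation 0.31. The following are assumptions: day-to-day error correlation 0.3, burning-type share 50% or 33% (the latter with a skewed variant), and two-sided testing. The June–July group effect was tested with standard errors clustered on patient. Covariance was estimated by REML, with 7,500 trials per size (five runs of 1,500).

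| Method | G = 19 | G = 24 |
|---|---|---|
| Plain sandwich, normal reference | 10.4% | 9.0% |
| × G/(G−1), normal reference | 9.5% | 8.3% |
| × G/(G−1), t(G−1) | 7.7% | 7.0% |
| CR2, normal reference | 7.1% | 6.7% |
| CR2, t(G−4) | 5.3% | 5.4% |
| REML model-based, normal reference | 6.6% | 6.3% |
| REML model-based, t(G−4) | 4.8% | 4.8% |

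The plain sandwich variance averaged 0.80 of the true variance at 19 patients and 0.83 at 24. With the covariance treated as known (4,000 trials per setting), the plain sandwich with a normal reference gave 9.4–10.5% at 19, 9.4–9.9% at 20 and 8.5–9.5% at 24.

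**4. Hand check.** If the variance is 0.80 of the truth and the statistic behaves like t(G−4), the rejection rate is 2 × P(t > 1.96 × √0.80) = 2 × P(t > 1.753). This is 10.0% on 15 degrees of freedom, 9.9% on 16 and 9.5% on 20.

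**5. What drives it.** A simpler patient-level simulation (20,000 null trials; outcome on group, baseline and burning type) separates the components:

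| Method | n = 19 | n = 24 |
|---|---|---|
| Sandwich × n/(n−1), normal | 10.5% | 8.9% |
| Sandwich × n/(n−4), normal | 7.8% | 6.9% |
| Sandwich × n/(n−4), t(n−4) | 5.9% | 5.6% |
| HC2, t(n−4) | 5.7% | 5.5% |
| HC3, t(n−4) | 3.5% | 3.7% |
| ML model-based, normal | 10.4% | 9.0% |

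ML model-based standard errors with a normal reference are as anti-conservative as the sandwich. Robust standard errors with proper scaling and a t reference come close to 5%. The fault is the uncorrected variance combined with the large-sample reference. In this simpler setting, a further run put G/(G−1) with t(G−1) at about 7–8.5%, and the corrected methods stayed near 5% under skewed errors.

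**The case against.** The strongest reply is that the error rate depends on choices the article does not make. A phrase that promises only robust standard errors is compatible with valid and invalid tests. Corrections and degrees of freedom are commonly left to an analysis plan, and one is said to exist. That stands, and it is why the point is conditional. It does not remove the point: the article does choose the estimator, and its common forms, including G/(G−1) with t(G−1), still exceed 5% at this size.

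A reader might infer that the primary test will certainly run at double its nominal level. The documents do not support that. With a bias-reduced sandwich and small-sample degrees of freedom the rate is about 5%. At the full 24 patients the uncorrected figure is about 8–9.5%, short of double.

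A reader might also infer that robust standard errors are themselves the mistake and should go. Step 5 shows otherwise. The article ties them to skewness, a fair motive, and they can be kept in corrected form.

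Lastly, family clustering might seem to support a still higher figure. Relatives do reduce the number of independent units, but neither the number of families nor the correlation within them is given, so any such figure would rest on invented inputs.

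**Conclusion.** The concern holds in conditional form. With 24 patients, about 19 to 20 after attrition, and two patient-level covariates besides group, the stated robust standard errors give a two-sided 5% primary test an actual level of about 8–10%, unless a small-sample correction with t-type degrees of freedom is applied. With G/(G−1) and t(G−1) it is about 6–8.5%. At 8–10% error, nominal 95% intervals cover about 90–92%. The same choice affects the other mixed-model outcomes.

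These sizes assume two-sided testing, the covariate and error distributions used in the simulations, and a day-to-day error correlation of 0.3. The direction follows from the small number of units, and the size agrees between the full-model simulation, the patient-level simulation and the hand check.

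**What to change.** State one of the following in the analysis plan for every between-group effect:

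- Keep robust standard errors, but use a bias-reduced sandwich (CR2 or similar), clustered on family where relatives are randomised together. Use a t reference with small-sample degrees of freedom: Satterthwaite, or about the number of patients minus 4. CR2 with a normal reference is not enough (about 7% in step 3).
- Or use REML model-based standard errors with Kenward-Roger or Satterthwaite degrees of freedom.

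A re-randomisation test that follows the stratified, family-clustered allocation would be a useful optional check on the primary p-value.

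The cost is a software option and a few lines of text. Intervals become wider. Compared with an uncorrected sandwich interval of average size, the ratio is roughly 2.131/1.753 = 1.22 at 19 patients and 2.086/1.753 = 1.19 at 24; much of this restores coverage that was missing. Compared with an interval that has the right variance and a 1.96 cut-off, it is 2.131/1.960 = 1.09 and 2.086/1.960 = 1.06. Power falls somewhat: on the plan's own inputs a t reference takes it from 79.6% to 75.1% at 10 patients per arm.

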### Study design and flowchart

The XPAND trial is a phase II two-armed parallel group RCT, with a delayed intervention control arm. Participants are randomised to either the intervention group who receive the XPAND intervention in addition to routine care between April and June 2018 or the control group who receive routine care in 2018 and then XPAND between April and June 2019. The delayed intervention control group is included to maximise information collection about the intervention due to the extremely rare nature of XP. For example, achievable sample sizes limit the ability to test between-group differences for the psychosocial outcomes with acceptable power and the delayed intervention group allows for intervention-related changes from baseline testing, which is less robust but still useful.

Patient flow through the study is described in figure 1. The baseline assessment takes place in April 2018 (t0). Post-randomisation assessments take place after completion of the intervention in June to July 2018 (t1), after a booster session in August 2018 (t2) and after a long-term follow-up in December 2018 (t3). All participants use a wrist-worn UVR dosimeter continuously from t0 to t2 and complete daily UVR protection diaries for 21 consecutive days at each assessment time point. At each assessment, participants additionally complete patient-reported outcomes. The t3 follow-up does not involve dosimetry or daily UVR protection diary. In addition, the delayed intervention control arm only completes three further assessments in April 2019 (t4) and June–July 2019 (t5), and December 2019 (t6) with dosimetry and daily UVR protection diary completed for 21 days at t4 and t5.

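### In the exploratory regression-discontinuity analysis, face dose between diary periods is filled with average photoprotection, so its variability and the shape of any step partly reflect the fill rule; the March to September window also conflicts with the dosimeter dates

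*Protocol article*

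**What the plan says.** Under Statistical analyses, the Protocol article describes a further exploratory analysis with dynamic regression models, to "evaluate changes in both level and variability in daily UVR exposure over time between March and September", "accounting for treatment using a regression discontinuity approach". The justification is dosimeter coverage: "This is possible as the dosimeter will be worn for the entire period". The diary covers only three-week blocks, so for D-to-F "it will also be necessary to calculate UVR D-to-F using average daily photoprotection during the pre and post diary intervals". The article adds that the main analysis differs, because it takes D-to-F directly from diary entries.

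Under Study design and flowchart, coverage is narrower: "All participants use a wrist-worn UVR dosimeter continuously from t0 to t2". The same section places t0 in April 2018 and t2 in August 2018, and has participants "complete daily UVR protection diaries for 21 consecutive days at each assessment time point". Under Primary outcome, D-to-F is the wrist dose weighted by the facial protection in use. Under Study design and flowchart, the intervention runs from April to June 2018, and under Primary outcome six of its seven sessions precede t1.

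**The concern.** D-to-F has two parts, wrist dose and protection. Between diary periods only the first is measured; the second is replaced by an average. This has two consequences for an analysis whose stated targets are level and variability.

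- **Variability.** A constant has no day-to-day variation, so D-to-F on filled days varies only through wrist dose. Diary and non-diary days then differ in variance by construction.
- **Level.** The protection part is flat within each filled stretch and can move only where the fill rule lets it. Six sessions are delivered before t1, so gradual change is plausible, and much of it would fall in weeks with no diary. The filled series cannot show when protection changed or how sharply.

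Separately, if the dosimeter is worn only from t0 to t2, there is no planned dosimetry in March or September. The pre-treatment segment is then little more than the April baseline.

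At stake is how an exploratory time-course result for face dose would be read. The primary and secondary estimates are not at stake.

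**Working it through.** The plan gives no figure of its own here to reproduce.

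**1. Coverage.** Diary days in 2018: 3 × 21 = 63 (t0, t1, t2). Whole calendar months from 1 April to 31 August are 153 days, an upper limit for t0 to t2. From 1 March to 30 September is 214 days.
- Filled share of dosimeter days: (153 − 63)/153 = 90/153 = 59%.
- Days of the stated window outside April to August: 214 − 153 = 61.

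**2. Variability.** On the log scale, log D-to-F = log wrist dose + log protection. If the parts are independent and protection carries a share s of the daily variance, a constant fill leaves SD ratio = √(1 − s). The documents give no value for s, so a range is shown:
- s = 10%: √0.90 = 0.95
- s = 25%: √0.75 = 0.87
- s = 50%: √0.50 = 0.71

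A simulation with assumed SDs of 0.8 (wrist) and 0.6 (protection) has s = 0.36/(0.64 + 0.36) = 36%. The SD on gap days fell from about 1.00 to 0.80, matching √0.64 = 0.80.

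**3. Step, gradual true change.** The sample size section targets a drop of 0.10 from 0.27 SED: 0.10/0.27 = 37%, a ratio of 0.63. Assume protection moves linearly on the log scale to that ratio between days 21 and 77 of 153, then stays flat. Fit one cut at day 21 with a separate level and slope on each side, without noise. Fitted step ratios:
- Unfilled series: 0.86. There is no true step; the value differs from 1.00 because a single post-cut slope misfits a ramp followed by a plateau. Stopping the fit at day 77 gives 1.00.
- Pre mean before the cut, post mean after it: 0.63.
- Mean of the two adjacent diaries in each gap: about 0.82 to 0.85 in slightly different set-ups, close to the unfilled value at this cut. The series then jumps at both edges of the t0–t1 gap, each time by √0.63 = 0.79.

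**4. Step, smooth drift and no intervention effect.** One simulated series per run, 600 runs per setting, SDs as in step 2, cut at day 41 or 79. Drift is the total change in log protection over the 153 days.
- Unfilled: false-step rate 4% to 7% at nominal 5%.
- Hard pre/post switch: 9% to 10% at drift 0, because error in the diary means is carried as if known; 12% to 14% at drift −0.4 (mean fitted step about −0.15); 20% to 26% at drift −0.8.
- Pooled adjacent diaries: 3% to 6%, so not inflated. The mean fitted step is still biased, in either direction: at drift −0.4, +0.055 for the day-41 cut and −0.045 for the day-79 cut; at drift −0.8, +0.127 and −0.106.

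**5. Dates.** Statistical analyses claims dosimetry throughout March to September; Study design and flowchart gives t0 (April) to t2 (August). Taken literally, both cannot be right.

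**The case against.** The strongest reply is that the stated target is daily UVR exposure, which the dosimeter measures directly. The wrist series needs no fill, so its level and variability are sound, and D-to-F comes in as an addition. That stands, and it limits the point to filled D-to-F. Even there the loss of variability is partial, because wrist variation remains.

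Second, the article names no switch point and does not say which average applies on which day; that detail may sit in the analysis plan. This also stands. A reader might infer that the fill necessarily manufactures the whole 37% target effect from a series with no step. The documents do not support that: 0.63 arises only under a hard pre/post switch, the same single-cut fit gives 0.86 with no fill, and pooling adjacent diaries gives about the same. What does not depend on the detail is that an average is constant over the days it fills.

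Third, there is a concurrent randomised control arm, which the calculations above omit. Drift common to both arms would tend to cancel between them, so the false-step rates describe a single series and not the between-arm contrast. A gradual change in one arm only would not cancel.

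Fourth, the analysis is labelled exploratory, the fill is disclosed, and the main analyses do not use it. The stated window may also be loose wording for April to August. These points lower the weight, but disclosing the fill does not make a step or variance in the filled series interpretable.

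**Conclusion.** The point holds for filled D-to-F and for the dates, and no further.

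- Up to 59% of dosimeter days would carry a constant protection value. Variability of D-to-F on those days is understated by about 5% to 29% in SD, for assumed protection shares of 10% to 50%. The 29% figure is the 50:50 case, not an estimate.
- The height of a step reflects a real contrast between diary means. Its timing and sharpness come from the fill rule. Under a hard switch a gradual change appears as a full jump (0.63 against about 0.86 unfilled, in the assumed scenario). Under pooling the fitted step can be biased either way and the jumps move to the diary edges.
- The March to September window conflicts with the t0 to t2 wear period by up to 61 days.

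A reader might go on to doubt the wrist-dose results or the primary comparison. Neither doubt is supported: wrist dose is measured, and the main analysis uses diary days only. The weight is low to moderate, and a correction is worthwhile because it is cheap.

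**What to change.** Three wording changes in the analysis plan:

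1. Base inference on level and variability on measured wrist UVR dose, within the days the dosimeter is worn (t0 to t2).
2. Restrict inference on D-to-F to the 63 diary days, or present the filled D-to-F series descriptively, with no test or interval for a step or for variability.
3. Reconcile the March to September window with the wear period in Study design and flowchart.

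No data collection or main analysis changes. The cost is that there will be no inferential D-to-F time course between the diary periods.
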